#### Acceptability

A semi-structured interview conducted with the participant, personal consultee and clinical staff will be used to determine the acceptability of trial experience and RVOS intervention. Questions will relate to key trial parameters such as experience of recruitment and randomisation and participant/staff burden (see Additional file 2 for acceptability questions).

#### Muscle mass and quality

To assess muscle mass, the rectus femoris (RF) muscle of both legs (in intervention participants) and only the right leg (control participants) will be imaged using B-mode ultrasound as previously described [21, 99] at baseline and on days 6 and 11 of study enrolment. Briefly, the participant will lie in a semi-recumbent position and the RF muscle will be scanned in the longitudinal plane on the anterior aspect of the thigh, two-thirds of the distance from the anterior superior iliac spine to the superior patella border. RF ultrasound images will be analysed using ImageJ software (NIH, Bethesda, MD, USA) by blinded investigators. Muscle mass will be quantified by assessing the RFCSA, and echogenicity will be measured to evaluate the changes in muscle quality as reported previously [100, 101]. Change over time in these measures will be compared between intervention and control participants, and changes in the treated leg and the untreated leg compared in those receiving the RVOS intervention.

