## Background

Increasing numbers of patients are being admitted to intensive care units (ICUs) and mortality rates have fallen [1–3]. However, survival comes at the expense of increased dependency and debility: 50% of patients of working age do not return to work; 70% require assistance with daily living activities in the year following discharge; and physical disability can persist for many years [4, 5]. The UK’s National Institute of Health and Care Excellence (NICE) has declared such post-ICU debility to be a public health issue [6].

Impaired quality of life and functional limitation partly result from ICU-acquired weakness (ICU-AW) [7–10]. This affects approximately 40% of adult ICU patients [11], with long-term ventilated or severely septic patients being most commonly and severely affected [12–16]. ICU-AW is associated with poorer outcomes: prolonged mechanical ventilation, increased ICU and hospital length of stay, increased hospital and post-discharge mortality rates, chronic functional disability and reduced quality of life among survivors [8, 17–20]. As a consequence, hospital health-care costs are 30% higher in those affected, with further excess costs relating to the need for rehabilitation, frequent re-admissions and social care upon discharge [18].

The pathophysiology of ICU-AW is multifactorial [10, 21–23]. Whilst neuropathies may occur [24], skeletal muscle wasting plays a central role [25]. The cross-sectional area of the rectus femoris (thigh) muscle (RFCSA) falls by an average of 18% in just 10 days in ventilated ICU patients, and to the greatest degree in those with the largest burden of organ failure [21]. This is underpinned by impaired skeletal muscle protein synthesis and, simultaneously, increased protein breakdown [21, 26], to which altered muscle metabolism [27] and disuse may contribute [23, 28]. The putative role of drugs such as corticosteroids, neuromuscular junction blocking agents and aminoglycoside antibiotics is contested [16, 29–31].

To date, no therapies exist for prevention or treatment of ICU-AW [32, 33]. Early mobilisation and physical activity regimes have proven ineffective [34–38], perhaps because muscle wasting has already occurred. There is thus growing interest in the early application of non-volitional interventions such as neuromuscular electrical stimulation, although proof of benefit remains lacking [38–42].

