### Secondary outcome measures

#### Feasibility

Table 3 presents the pre-specified feasibility criteria that will be assessed.

**Table 3 Tab3:** Feasibility criteria of the study

Trial process	Outcome measure	Feasibility criteria
Screening	Percentage of potentially eligible patients being missed	< 55% of potentially eligible patients being missed
Consent	Percentage of personal consultee/participants agreeing to enrolment	> 75% of personal consultees/participants agreeing to enrolment
Recruitment rate	Number of patients recruited	Recruit 30 patients within 16 months
Randomisation	Demographic and severity of illness in the intervention and control arms	Balanced demographic and severity of illness in intervention and control arm participants
Delivery of intervention	Percentage of RVOS sessions performed out of the total possible sessions	80% of the scheduled RVOS sessions performed
Retention rate	Percentage of patients that remain on the ICU for the full 10 days of study enrolment	> 50% of enrolled patients remain on the ICU for the full 10 days of study enrolment
Outcome measure assessments	Percentage of outcome measure assessments performed within 24 h of the scheduled time Percentage of quality-of-life questionnaires completed at 90-day follow-up	100% of RFCSA ultrasound measurements performed within 24 h of the scheduled time > 75% of vascular, strength and functional capacity measures performed within 24 h of the scheduled time > 75% of surviving patients complete the quality-of-life questionnaires at 90-day follow-up
Electronic case report form data collection	Percentage of missing outcome and clinical data	< 10% missing outcome data including ICU and hospital length of stay and survival < 10% missing clinical data obtained from clinical medical notes and electronic patient records, such as severity of illness scores and requirement for organ supportive therapies

*ICU* intensive care unit, *RFCSA* rectus femoris cross sectional area, *RVOS* repetitive vascular occlusion stimulus

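### The muscle-scan method names the longitudinal plane but derives a cross-sectional area, which that plane cannot give; probably a wording slip, to be corrected and checked against the stored images

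*Protocol article*

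**What the plan says.** The Muscle mass and quality section describes a single ultrasound acquisition for the rectus femoris. The muscle "will be imaged using B-mode ultrasound as previously described [21, 99] at baseline and on days 6 and 11 of study enrolment". A short summary of the technique follows: the muscle "will be scanned in the longitudinal plane on the anterior aspect of the thigh", at a single level, "two-thirds of the distance from the anterior superior iliac spine to the superior patella border". The images go to blinded investigators, who measure them in ImageJ, and the quantity wanted is explicit: "Muscle mass will be quantified by assessing the RFCSA". Echogenicity is measured as well, for muscle quality.

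The Background spells out what RFCSA is: "The cross-sectional area of the rectus femoris (thigh) muscle (RFCSA) falls by an average of 18% in just 10 days in ventilated ICU patients". The abbreviation is expanded in the same way under Table 3 and in the abbreviation list.

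RFCSA is used in three further places. Table 3 sets a criterion of "100% of RFCSA ultrasound measurements performed within 24 h of the scheduled time", against more than 75% for the vascular, strength and functional measures. The Statistical analysis section names it first among the repeated outcomes for the mixed model. The Abstract's Discussion and the Secondary objectives say that the trial's data will inform the design and powering of a later trial.

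**The concern.** The acquisition instruction and the derived quantity do not fit together. A cross-sectional area is traced on an image perpendicular to the muscle's long axis. A longitudinal image contains that axis. It shows how long and how thick the muscle is in one slice, and it carries no information on width.

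At stake is the muscle-mass evidence that the pilot is meant to pass on. RFCSA is the only muscle-mass measure named, and both the between-arm comparison and the treated-versus-untreated-leg comparison depend on it. Someone repeating the method as printed would collect images on which it cannot be measured.

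**Working it through.** The protocol gives no figure of its own on this point to reproduce. The check compares the text with itself and then applies simple geometry.

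**Text against text**

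| Item | What the article gives | Where |
|---|---|---|
| Plane of the scan | longitudinal | Muscle mass and quality |
| Level of the scan | one point, two-thirds of the way down the thigh | Muscle mass and quality |
| Quantity derived | RFCSA | Muscle mass and quality |
| Meaning of RFCSA | cross-sectional area of the rectus femoris | Background; Table 3 footnote; Abbreviations |
| Any transverse muscle scan | none described | whole article |
| Technique in full | deferred to two cited sources, not at hand | Muscle mass and quality |

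The plane and the quantity conflict within one paragraph, and nothing elsewhere in the article resolves the conflict.

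**Can thickness stand in for area?** As an illustration only, treat the cross-section as an ellipse:

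CSA = (π/4) × width × thickness.

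The dimensions below are assumed, because the article gives none. Thickness is held at 1.5 cm, which is what a longitudinal view would show:

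- width 2 cm: 0.7854 × 2 × 1.5 = 2.36 cm²
- width 3 cm: 0.7854 × 3 × 1.5 = 3.53 cm²
- width 4 cm: 0.7854 × 4 × 1.5 = 4.71 cm²

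The same longitudinal reading fits areas that differ by a factor of 4.71 / 2.36 = 2.0.

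**Can change in thickness stand in for change in area?** Take the Background's 18% fall in RFCSA. With proportional losses w in width and t in thickness, (1 − w)(1 − t) = 0.82, so t = 1 − 0.82 / (1 − w):

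- w = 0: t = 18%
- w = 9.45%: t = 9.44% (loss shared about equally)
- w = 18%: t = 0%

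So an 18% loss of area could show as a thickness loss anywhere from 0% to 18%. A longitudinal scan fixes neither RFCSA nor its change over time.

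**The case against.** The strongest reply is that this is a slip of wording. The sentence is announced as a brief summary of a technique described in two cited sources, and the 18% fall in RFCSA in the Background is cited to one of those same sources. The intended quantity is therefore not in doubt. Fixing a single level on the thigh also suits a transverse slice, and an investigator asked to trace an area would soon notice an image with no cross-section in it. Recruitment closed in February 2019 and the article appeared in July 2019, so no enrolment scan was taken from this printed sentence. All of this stands, and it makes a slip the likelier explanation. It does not make the sentence correct: the article chose to summarise the method, and the summary contradicts the measurement that follows.

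Several stronger readings are tempting, and the documents do not support them:

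- **That the RFCSA data are lost.** A reader might count 32 × 3 = 96 right-leg scans and 16 × 3 = 48 left-leg scans as unusable. Nothing shows that any image was acquired longitudinally. The counts are also only nominal, since recruitment runs until 32 patients have survived the ICU and some scans will be missed through death or discharge.
- **That the two sites scanned differently.** Nothing suggests this. The Recruitment and randomisation process section gives outcome assessment to a research assistant.
- **That the Table 3 criterion fails.** That criterion concerns completion and timing of the scans, not the area obtained from them.
- **That a primary result is affected.** The primary outcomes are serious adverse events and pain scores. RFCSA is secondary, and its analysis is for direction and magnitude only. Echogenicity is not shown to be affected either.

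**Conclusion.** The point holds as an error in the stated method. Taken literally, the method cannot produce RFCSA, and no other part of the article supplies the missing transverse view. This rests only on the article's own expansion of RFCSA and on the geometry of the two planes. The ellipse and its dimensions illustrate the size of the ambiguity, and the conclusion does not depend on them.

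Its reach is limited. It concerns one secondary, exploratory outcome and leaves the safety and tolerability conclusions untouched. It is still worth correcting, because that outcome is the only muscle-mass measure that the pilot offers to the design of the next trial. Whether any stored image is affected cannot be told from the article.

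**What to change.** 1. If the images were acquired transversely, correct the sentence to the transverse plane, perpendicular to the long axis of the thigh at the stated two-thirds point. If they were not, state the plane that was used.
2. Before RFCSA is analysed, confirm that the stored images from both sites are transverse.
3. Report any longitudinal images separately, under the name of what they measure, and do not label the result RFCSA.

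The cost is a one-word correction and a check of images already on file. No change to sample size, visit schedule or analysis model is needed.

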#### Arterial vascular measures

Arterial vascular function will be assessed at the same time points as muscle evaluation, using techniques previously described [102]. The diameter and blood flow velocity of the right superficial femoral artery at rest and immediately following 5 min of ischaemia will be measured using B-mode and pulse Doppler ultrasound imaging, respectively. Ischaemia will be induced by application of a pneumatic cuff to the right thigh and inflation to 200 mmHg cuff pressure. Blinded investigators will analyse the diameter and blood flow velocity using the commercially available software Brachial Analyzer (Vascular Research Tools 5; Medical Imaging Applications, LLC, Coralville, IA, USA) to assess flow-mediated dilation (FMD) and reactive hyperaemic response, surrogate markers of vascular health. The reactive hyperaemic response is a transient increase in blood flow in response to ischaemic stimulus, and a marker of vasodilator capacity of resistance vessels. FMD assesses endothelial-dependent vasodilation of the conduit artery in response to increased blood flow and internal wall shear stress. The resting SFA diameter and blood velocity, reactive hyperaemic response and FMD will be compared between intervention and control participants at each time point.

#### Muscle strength

On days 6 and 11 and at ICU and hospital discharge, the grip strength of the dominant hand will be assessed using a handgrip dynamometer (Takei Scientific Instruments Co. Ltd, Niigata City, Japan) and manual muscle strength evaluation of the bilateral six upper and lower limb muscle groups (shoulder abductors, elbow flexors, wrist extensors, hip flexors, knee extensors and foot dorsiflexors) performed using the Medical Research Council Sum Score (MRC-SS) [103]. Strength assessments will only be performed if the participant is sufficiently alert and free from delirium.

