#### Physical function

Mobility will be assessed in the ICU on days 1, 6 and 11 of study enrolment (or at ICU discharge, whichever is earlier) and at hospital discharge, using the ICU Mobility Scale, a validated measure with excellent clinometric properties [104, 105]. In addition, functional assessment (‘timed up and go’ and ‘sit to stand’) will be performed at hospital discharge. ‘Timed up and go’ will involve measuring the time taken to stand up from a standard chair, walk a 3-m distance at normal pace and return to the chair; for ‘sit to stand’, the number of times that the participant is able to completely stand upright from a standard chair and sit back down fully within 30 s will be assessed. Due to the study population being frail, use of aids will be permitted and documented.

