#### Clinical outcomes

Clinical outcomes between participants in the intervention and control arms will be compared: incidence and duration of delirium; incidence, duration and severity of acute kidney injury (assessed using the AKIN classification) [106]; duration of specific organ support (mechanical ventilation, renal replacement therapy, mechanical or pharmacological cardiovascular support); days alive and without a ventilator in the first 28 days of hospital stay; length of ICU and hospital stay; and hospital and 3-month mortality.

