Repeated outcome measures such as the RFCSA and echogenicity, superficial femoral artery measures (resting diameter and blood flow, FMD and reactive hyperaemic response), ICU mobility score, MRC-SS and handgrip strength data will be analysed separately as the response variable in a general linear mixed model using SAS PROC MIXED, with group (the dichotomy of standard care or RVOS), site, baseline measure, time and group × time interaction as fixed effects and subject as random effects. Appropriately selected covariates will be included in the model as fixed effects to adjust for the variability caused by these covariates.

All statistical analyses will be performed by the Trial Statistician at Surrey Clinical Trials Unit (CTU) according to a pre-specified Statistical Analysis Plan, which will be finalised and signed off before the database lock.

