## Discussion

This study will be the first to assess the safety, tolerability, feasibility and acceptability of RVOS in ICU patients. The effect of RVOS on muscle mass atrophy and weakness, and on arterial dysfunction observed in ICU patients, will also be explored.

Thirty-two ventilated critically ill patients with at least two other organ failures will be recruited to the study. Multiple organ failure patients were chosen as the study population because these patients undergo more pronounced muscle wasting (16% decrease in the RFCSA compared to 3% in single organ failure patients within 7 days of ICU admission) [21].

RVOS will be performed using equipment conventionally and safely used for vascular disease diagnostics and routinely used during vascular and orthopaedic operations. Control participants will receive standard care and no sham treatment (repeated cuff inflation at lower pressure) so as to avoid any detrimental impacts of isolated venous occlusion. Participants will thus not be blinded in the study. However, this is unlikely to introduce bias to the objective measures as muscle and arterial ultrasound images will be anonymised and analysed blinded to subject identity, study time points and group allocation.

The tolerability of RVOS cannot be assessed when participants are ventilated and sedated. Even when participants are extubated and off sedation, delirium (an acute brain dysfunction) is common in critically ill patients and can influence the VAS score. CAM-ICU assessment will be performed and the mental state of the participant during the RVOS session will be recorded to observe any effects of delirium on the VAS score.

Ultrasound assessments of muscle mass and quality and arterial function can be performed when participants are sedated; however, muscle strength and physical function measures are volitional assessments and require the participant’s full attention and cooperation. Therefore, sedation, lack of willingness to participate or lack of mental capacity due to delirium can prevent these outcome assessments. These measures will therefore only be performed when the participant is off sedation and CAM-ICU negative; this could lead to the time points when the strength and physical function assessments are performed varying between participants.

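### Timed up and go, MRC-SS and handgrip are compared only among patients who can be tested, so the estimated effect is biased if the arms differ in who becomes testable

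*Protocol article*

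**What the plan says.** All references are to the Protocol article.

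- **Who is tested.** Muscle strength: "Strength assessments will only be performed if the participant is sufficiently alert and free from delirium". The Discussion extends the rule to physical function: "These measures will therefore only be performed when the participant is off sedation and CAM-ICU negative". It also gives the obstacles: "sedation, lack of willingness to participate or lack of mental capacity due to delirium can prevent these outcome assessments".
- **When.** Muscle strength: "On days 6 and 11 and at ICU and hospital discharge, the grip strength of the dominant hand will be assessed"; MRC-SS follows the same schedule. The baseline list under Study protocol names the ICU mobility score but no MRC-SS or handgrip.
- **How analysed.** Statistical analysis: "MRC-SS and handgrip strength data will be analysed separately as the response variable in a general linear mixed model", with a baseline measure among the fixed effects. Timed up and go is compared by independent-sample t test.
- **Timed up and go.** Physical function defines it as "measuring the time taken to stand up from a standard chair, walk a 3-m distance at normal pace and return to the chair", done at hospital discharge with aids permitted.
- **Consequence acknowledged.** The Discussion draws only one: "this could lead to the time points when the strength and physical function assessments are performed varying between participants".
- **Purpose.** Statistical analysis says the inferential comparisons serve to identify the directions and magnitudes of effects, not significance.

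**The concern.** Being awake and free from delirium on day 6 or 11 is reached after randomisation and depends on how the patient is recovering. The protocol compares "incidence and duration of delirium" and duration of ventilation between arms, so it treats the gateway to strength testing as something that could differ by treatment. A comparison of tested patients is then a comparison of two selected groups.

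A mixed model allows for missing values only if untested patients resemble tested ones given the terms in the model. Without an earlier strength value it has little to work from. An added baseline test would face the same rule, when the protocol expects most patients to be sedated at enrolment.

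Timed up and go is the clearest case. A survivor who cannot walk the distance has no time, so the worst outcome on that test is left out of the t test instead of counting against the arm.

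At stake is the direction and size of effect carried into the design of the larger trial.

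**Working it through.** **Inputs.** The documents give 16 ICU survivors per arm (Sample size rationale) and a feasibility target of more than 75% of vascular, strength and functional measures performed on time (Table 3). They give no mean, SD, effect size or testable share for strength, so there is no planned figure to reproduce. Every MRC-SS value and share below is an assumption.

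**1. Break-even, free of any distribution.** Let q0 patients per arm be testable regardless of treatment, with control mean m0 and RVOS mean m0 + d. Let e further patients, with mean m1 below m0, become testable only under RVOS. Then

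observed difference = [q0·d − e·(m0 − m1)] / (q0 + e),

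and the sign reverses when e/q0 > d/(m0 − m1). For d = 2:

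| Gap m0 − m1 | Break-even e/q0 | Extra patients needed if 10 to 13 controls are tested |
|---|---|---|
| 5 | 0.40 | 5 to 6 |
| 10 | 0.20 | 3 |
| 15 | 0.13 | 2 |
| 20 | 0.10 | 2 |

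Example with both arms above 75%: 13 of 16 against 15 of 16 tested, gap 15. (13×2 − 2×15)/15 = −4/15 = −0.27. With gap 10 the same counts give (26 − 20)/15 = +0.40, so the sign holds.

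The same algebra applies to timed up and go, with completion times for scores and the sign turned round because longer is worse.

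**2. Model in which weaker patients are less often testable.** Latent strength L is standard normal. MRC-SS = 42 + 10L, plus 2 under RVOS, limited to 0 to 60. The chance of being testable is 1/(1 + exp(−(a + L))), with a chosen to give each share. The true difference among all patients is +1.9. Observed among the tested, by numerical integration:

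| Control testable | RVOS testable | Observed difference |
|---|---|---|
| 40% | 40% | +1.8 |
| 40% | 60% | +0.3 |
| 40% | 70% | −0.45 |
| 75% | 75% | +1.9 |
| 75% | 80% | +1.5 |
| 75% | 85% | +1.1 |
| 75% | 90% | +0.7 |

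From 75% in control, the sign changes only at about 98% under RVOS.

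**3. A second model.** Mean 38, SD 12, with testability driven by the patient's actual strength and a steeper slope. At 59% against 77% testable, a true +1.9 appears as −0.45, and a trial of 16 per arm shows the wrong sign in 54% of runs, against 32% if everyone could be tested. If RVOS acts on testability only through strength, a true +1.9 appears as +1.2 to +1.6 across the shallower and steeper slopes: attenuated, not reversed.

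**4. Ranking untestable patients lowest.** In the model of step 2, the probability that an RVOS patient ranks better is 0.51, 0.60 and 0.65 at 40% against 40, 60 and 70%. With no strength effect at all it is still 0.59 and 0.63 at 40% against 60 and 70%. With a true benefit and everyone tested it is 0.56. The rank result therefore mixes wakefulness with strength.

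**The case against.** The strongest reply is that handling of untestable patients belongs in the SAP, which the protocol says will be signed off before database lock. That would answer a complaint about silence. Here the article itself fixes who is tested and which analysis is run on the resulting values, and that combination gives the selected contrast. An SAP rule could still repair it.

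Other replies stand in part:

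- **Much is already collected.** Assessment completion is a feasibility outcome, delirium and ventilation are compared by arm, covariates may be added, and strength is tested again at ICU and hospital discharge. The Discussion's remark on varying time points suggests that some tests are delayed, not lost. None of this gives a value to a patient who is never testable or shows the testable share beside the estimate.
- **Non-walkers are not wholly ignored.** Sit to stand is a count on which a patient who cannot stand can score 0, and the ICU Mobility Scale covers immobile patients. It would be wrong to infer that the weakest survivors never count; the gap is specific to timed up and go.
- **The sedated majority is misread if applied later.** That statement, under Recruitment and randomisation process, concerns capacity to consent at enrolment. It does not show what share is untestable on day 6 or 11.
- **No effect on wakefulness is proposed.** The Background describes muscle and vascular effects only, so a large difference in testable shares is possible but not predicted.
- **Worst-rank scoring changes the question.** This is correct, and limits it to a sensitivity analysis.

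**Conclusion.** The point holds as a conditional bias. Followed as written, the plan estimates effects among testable patients for MRC-SS and handgrip, and among patients able to complete the walk for timed up and go. If the arms differ in who is testable, direction and magnitude are both affected.

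A reader might infer that the plan will report a benefit as harm. The documents do not support that. With 75% of controls testable, the assumed model gives attenuation from +1.9 to between +1.5 and +0.7. Reversal needs a large difference in testability, such as 40% against 70%, or extra patients much weaker than those already tested, such as 15 points in the 13 against 15 example. If RVOS changes strength alone, the estimate is only attenuated. The 75% is a feasibility target, not a forecast, so the true position within these ranges is unknown.

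These are exploratory secondary outcomes. The primary safety and tolerability conclusions are untouched. The change is worth making because direction and magnitude are the stated use of these analyses.

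**What to change.** 1. **Timed up and go:** analyse as walking speed, with patients unable because of physical limitation scored 0. Those not tested for another reason, such as refusal or delirium, are reported separately and not scored 0.
2. **MRC-SS and handgrip:** keep the mixed model. Beside every estimate, show the number testable by arm and time point, with the reason for non-assessment (sedation, delirium, weakness, refusal, discharge, death). Describe the estimates as conditional on being testable.
3. **Sensitivity analysis only:** add a between-arm rank comparison with living untestable patients placed lowest, labelled as combining wakefulness and strength.

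The cost is some SAP wording, one table and one extra analysis per strength outcome. The reason for non-assessment must be on record. Recruitment is reported complete, so where it was not captured it would have to be drawn from the daily clinical data and delirium records, with the remainder shown as unknown. The rank result cannot be read in strength units and is not a pure strength effect.
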